### **3.7. Statistical analyzes**

All statistical analyzes will be performed by an independent examiner, blinded to the group allocation. Each participant will be assigned with a unique code. All analyses will be performed using SPSS (SPSS Inc., Chicago, IL, USA). The normality of data distribution will be verified for all continuous numeric variables. Descriptive statistics will be calculated for all outcomes. The effects of the interventions will be analyzed from the collected data using intention-to-treat. Data from the last available evaluation will be used for missed sessions. Two-way ANOVA with repeated measures (2\*3) will be used to evaluate the differences between groups, considering the time factor (considering baseline, post-intervention, and 4-week follow-up), for the variables: inspiratory and expiratory muscle strength, respiratory muscle endurance, peak cough flow, and exercise capacity. The level of significance will be set at 5% and adjusted for multiple comparisons. Data distribution and equality of variance will also be analyzed, to ensure the parametric analysis has been applied correctly. The effect sizes will be calculated to determine the magnitude of the differences between the groups. The differences between the two mean values will be expressed in units of their SD, expressed as Cohen's d, or mean results for the experimental group minus the mean results for the control group, divided by the SD of the control group. Effect sizes between 0.2 and 0.5 will be considered small; between 0.5 and 0.8, medium; and above 0.8, large.

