#### **3.6. Sample size calculation**

The sample size calculation was performed considering the primary outcome measures (inspiratory and expiratory muscle strength). The effect size for inspiratory muscle training was derived from an RCT with a similar population and intervention. Considering a significance level ( $\alpha$ ) of 5% and a power of 0.80, thirteen participants per group are required (26 participants). The effect size for expiratory muscle training was also derived from an RCT with a similar population and intervention. Considering a significance level ( $\alpha$ ) of 5% and a power of 0.80, fourteen participants per group are required (28 participants). Therefore, a sample size of 28 individuals (14 in each group)

was defined (the largest sample size calculated). Assuming an expected dropout rate of 20%, a total sample size of 34 individuals was set (17 in each group).

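### The planned 2×3 ANOVA for MIP and MEP takes baseline as an outcome level and names no primary term or time point, so the sample size cannot be tied to a test

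*Protocol*

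**What the plan says.** Protocol section 3.7 gives one model for MIP, MEP, endurance, peak cough flow and exercise capacity: "Two-way ANOVA with repeated measures (2\*3) will be used to evaluate the differences between groups". The levels of the time factor follow: "considering baseline, post-intervention, and 4-week follow-up". On multiplicity it says "The level of significance will be set at 5% and adjusted for multiple comparisons", without naming the family of comparisons or the method. It also plans standardised between-group effect sizes, again without a time point, and an independent analyst blinded to allocation.

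Section 3.4 schedules measurements at weeks 0, 8 and 12. The Abstract and sections 2.0, 3.4, 3.5.1 and 3.7 name MIP and MEP as primary, or describe their measurement and analysis, without singling out one visit.

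Section 3.6 opens with "The sample size calculation was performed considering the primary outcome measures". For MIP: "The effect size for inspiratory muscle training was derived from an RCT with a similar population and intervention", then "of 5% and a power of 0.80, thirteen participants per group are required (26 participants". For MEP: "The effect size for expiratory muscle training was also derived from an RCT with a similar population and intervention", then "of 5% and a power of 0.80, fourteen participants per group are required (28 participants". It states no effect size, SD, within-person correlation, statistical test or visit.

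**The concern.** Baseline is measured before the allocation envelope is opened (section 3.2), so it cannot carry a treatment effect. Making it a level of the outcome factor leaves several candidate answers to the primary question:

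- a group effect averaged over a visit at which no difference is expected;
- a 2-df interaction that combines the end-of-training effect with what remains a month after training stops;
- separate contrasts at week 8 and week 12, which ask about training effect and retention respectively.

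These can disagree, and their power differs. If none is named in advance, the choice can be made after the results are seen. The blinded analyst limits choices driven by direction but does not fix the contrast. A significant interaction would also leave the reader without the quantity of interest: how far training shifted MIP or MEP at the end of the programme, and with what precision.

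**Working it through.** **The plan's own figure.** The 13 and 14 per group cannot be reproduced, because no effect size is given. If a two-sided two-sample t-test at 5% and 80% power is assumed, 13 per group implies d = 1.145 and 14 implies d = 1.100. One-sided, they imply 1.00 and 0.97. Any n yields some d in this way, so the result does not identify the test that was used.

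**Inputs.** From the protocol: n = 14 per arm, alpha 5%, visits at weeks 0, 8 and 12. Assumed: two-sided testing; d = 1.10 in SDs of the baseline-to-week-8 change; equal variance (set to 1) and equal correlation ρ between visits, with ρ = 0.5, 0.7 or 0.8; a fraction r of the week-8 effect kept at week 12. No adjustment for multiple comparisons is applied.

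The SD of change is √(2(1−ρ)), so the week-8 effect is Δ = 1.10 × √(2(1−ρ)) = 1.100, 0.852 and 0.696.

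**Group main effect.** The expected difference is (0 + Δ + rΔ)/3 = Δ(1+r)/3. That is 2/3 of Δ at r = 1, 1/2 at r = 0.5 and 1/3 at r = 0. A person's mean over three visits has SD √((1+2ρ)/3).

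- Example, ρ = 0.5, r = 1: 0.733/0.816 = 0.898; noncentral t with 26 df gives power 0.63.
- Example, ρ = 0.8, r = 1: 0.464/0.931 = 0.498; power 0.25.

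**Interaction (2 and 52 df).** The noncentrality is λ = n·d²·[1 + r² − (1+r)²/3], which does not depend on ρ when d is on the change scale. Here n·d² = 14 × 1.21 = 16.94.

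- r = 1 or r = 0: 16.94 × 2/3 = 11.29; power 0.84.
- r = 0.75 or r = 0.25: λ = 9.18; power 0.75.
- r = 0.5: 16.94 × 0.5 = 8.47; power 0.72, the minimum.

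**Week-8 ANCOVA (25 df).** The standardised effect is Δ/√(1−ρ²) = 1.10 × √(2/(1+ρ)) = 1.27, 1.19 and 1.16. Simulated power is about 0.89, 0.84 and 0.83, and does not depend on r.

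| Kept at week 12 | Group effect, ρ 0.5 to 0.8 | Interaction | Week-8 ANCOVA, ρ 0.5 to 0.8 |
|---|---|---|---|
| All | 0.63 to 0.25 | 0.84 | 0.89 to 0.83 |
| Half | 0.40 to 0.16 | 0.72 | 0.89 to 0.83 |
| None | 0.21 to 0.10 | 0.84 | 0.89 to 0.83 |

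**Sensitivity to the scale of d.** If d = 1.10 is instead in week-8 SDs (simulation, 20,000 runs per setting), then over ρ = 0.5 to 0.8:

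- ANCOVA has 0.89 to 0.99;
- the interaction has 0.84 to 0.998 with the gain kept and 0.73 to 0.99 with half lost;
- the group effect has 0.63 to 0.52 with the gain kept and 0.41 to 0.33 with half lost.

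At ρ = 0.3 the interaction has 0.69 (kept) and 0.55 (half lost), against 0.82 for ANCOVA. The absolute figures move; the weakness of the group effect remains.

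**The case against.** The strongest defence is that section 3.7 speaks of group differences in relation to the time factor, which most naturally means the interaction. That test is valid in a randomised trial, and nothing here shows bias or an inflated type I error. Between-group effect sizes and a multiplicity adjustment suggest that pairwise follow-up is foreseen. A separate SAP may exist, and follow-up contrasts, covariates and model form are commonly left to it. The absence of a baseline covariate is therefore not an error in itself, and ANCOVA is partly an efficiency preference. The half-fade case is also the least favourable one for the interaction.

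Most of this stands, and it removes two stronger readings. A reader might infer that the trial was powered on a two-group test and will be analysed with another. Section 3.6 names no test, and inferring one from the n per group is circular. A reader might also infer that the baseline data are wasted. That is wrong for the interaction, which uses baseline through within-person change and roughly equals ANCOVA at ρ of 0.7 or more when the gain is fully kept or fully lost.

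What the defence does not supply is a primary term or time point. The protocol fixes the ANOVA and its levels itself, and its wording still admits the diluted group effect.

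**Conclusion.** The point holds in a limited form and should be fixed; it does not invalidate the design. The protocol makes baseline an outcome level, leaves the primary term and visit open for MIP and MEP, and gives a sample size that cannot be linked to any term of the ANOVA.

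The size of the problem depends on which term is read. The group effect is the poor choice: power 0.63 at best and 0.10 at worst on the change scale. Against the interaction, the gain from a baseline-adjusted week-8 contrast is clear with partial fade (0.72 against 0.83 to 0.89) or low ρ, and negligible at ρ of 0.7 or more with full retention or complete fade. Even then the interaction does not by itself give the week-8 difference.

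All power figures rest on assumed d, ρ and retention; the protocol gives none of them. A definite power deficit therefore cannot be charged to this plan.

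**What to change.** In section 3.7, state that the primary analysis is the baseline-adjusted difference between groups at week 8, separately for MIP and for MEP, each with a 95% confidence interval. Either ANCOVA or a linear mixed model with weeks 8 and 12 as outcomes and baseline as covariate will do. Make the week-12 contrast secondary. State that neither the group main effect nor the omnibus interaction is the test of efficacy.

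In section 3.6, give the effect size, its scale (SD of the outcome or of change), the assumed correlation and the test behind the number per group, all for that week-8 contrast.

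The cost is protocol wording and one degree of freedom for the covariate. All three visits are already scheduled, so no new data are needed.
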